**Fig. 1 Fig1:**
[figure not shown]
Location of pericardium 6 (P6). The illustration is used to train the staff. The grey dot indicates the position of P6 between the flexor carpi radialis and the palmaris longus tendons

P6 stimulation ends right before emergence from anaesthesia. Opaque dressings are applied at the (potential) sites of stimulation in both groups to ensure patient and observer blinding.

##### Postanaesthesia care unit (PACU)

Postoperatively, patients are transferred into the PACU. Treatment of postoperative pain and other symptoms is performed according to usual care but documented in the CRF. Nausea and vomiting and potential antiemetic medication administered in the PACU are of special interest.

##### Ward (first postoperative day)

On the first postoperative day (22–26 h after the end of anaesthesia), patients are visited by a member of the study team. This person is blinded to the type of treatment and without knowledge of the anaesthesia technique performed or perioperative medication administered. Patients receive questionnaires targeting the occurrence of nausea and vomiting and overall well-being. Patients are asked to complete these forms by themselves, but help can be provided if necessary.

#### Criteria for discontinuing or modifying allocated interventions {11b}

The intervention will take place during anaesthesia. If PONV is occurring afterwards, routine care will be performed and documented.

#### Strategies to improve adherence to interventions {11c}

Antiemetic prophylaxis and therapy are documented as described before. The anaesthesiologists’ self-commitment is used to minimise bias regarding the antiemetic therapy. Any deviations from the specified prophylaxis are documented, stating the reason for the deviation. Anaesthesiologists are trained with a standardised procedure (see Fig. 1) to avoid poor implementation of P6 stimulation and insufficient stimulation time of P6.

#### Relevant concomitant care permitted or prohibited during the trial {11d}

n/a: Routine care is performed.

#### Provisions for post-trial care {30}

To the best of our knowledge, there is no harm documented in the literature by the materials used for acustimulation.

### Outcomes {12}

#### Primary endpoint

The primary outcome measure for this study is the incidence of PONV within a 24-h observation period. PONV is defined as nausea, retching, vomiting, or the need for any antiemetic medication during the observation period.

#### Secondary endpoints

Secondary endpoints include the followingThe intensity of PONV during the 24 h observational period is classified using the ‘postoperative nausea and vomiting Intensity Scale’ (PIS) [24],The patient-reported outcome of perioperative quality of life.The incidence and severity of adverse reactions caused by the different combinations of antiemetic drugs.

These endpoints are determined by using the following specific questionnaires:▪ ‘Patient Evaluation in the Perioperative Phase’ (PPP33)▪ Adverse effects via the ‘Postoperative side effects questionnaire’ (PON-F)

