##### Pharmacological antiemetic prophylaxis

The study aims to identify the effectiveness of P6 acustimulation along with conventional antiemetics administered intraoperatively. Thus, there is a high risk of bias that techniques for P6 stimulation might interfere with the pharmacological measures against PONV and vice versa. Special efforts are undertaken to ensure unbiased and comparable use of antiemetics in both groups. Comprehensive information is provided to the anaesthesiologists which highlight the need for ‘usual care’ in both groups. Additionally, all anaesthesiologists are required to fill in a document for personal ‘self-commitment’. With this form, the anaesthesiologist determines and documents the antiemetic prophylaxis that is suitable and will be administered to the individual patient (for the form, see Additional file 1). This part of the documentation form is filled out and signed by the anaesthesiologist and the attending nurse (four-eyes principle) before group allocation is revealed. This allows the determination of pharmacological interventions against PONV independent of the result of the randomisation procedure.

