##### Antiemetic medication

The anaesthesia staff administers antiemetics according to their self-committed individual medication plan. One of a combination of the following measures may be used:▪ Dexamethasone 4–8 mg▪ 5-HT3-antagonists (e.g. ondansetron 4–8 mg, granisetron 1 mg)▪ Droperidol 0.5–1.5 mg▪ Haloperidol 0.5–1.5 mg▪ Metoclopramide 10–20 mg▪ Dimenhydrinate 50–70 mg▪ Fosaprepitant (no dose restriction)▪ Use of propofol for total intravenous anaesthesia▪Omission of nitrous oxide

The attending anaesthesiologist is free to administer any of the above-mentioned interventions and to combine drugs of different pharmacologic classes (e.g. due to high individual risk of the patient for PONV) but also to withhold antiemetic medication (e.g. if a low risk for PONV is present). Furthermore, the time of administration can be chosen by the overseeing anaesthesia team. The chosen prophylaxis (drug(s), dose, and time of administration) is recorded in a paper-based case report form (CRF).

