##### Intervention

The anaesthesia team is allowed to open the opaque randomisation envelope after completing the self-commitment. This envelope includes information whether the patient is allocated to the control or the intervention group.

Patients allocated to the intervention group receive acustimulation at both forearms at the P6 point immediately after the induction of anaesthesia. Pressure is applied to the needles for about 15 s at the beginning and the end of the intervention to stimulate P6. The applied force should cause the needle tip to reach a depth of 0.5 to 1 cun (traditional Chinese measuring unit) [21]. Anaesthesiologists can also use acupressure bands for intervention instead of acupuncture needles. The intervention and its duration of administration are recorded.

The control group receives only the designated antiemetic prophylaxis according to the self-commitment.

The P6 acupoint is located 2 cun [22] from the distal palmar crease between the flexor carpi radialis tendon and the palmaris longus tendon on the volar surface of both forearms [23]. All anaesthesiologists were informed about the study and were provided with verbal and written information on anatomical location of the P6 stimulation point and the need for applying pressure to the needle. An information sheet (including the illustration from Fig. 1) was available in all operating rooms. For acupuncture, Seirin® New Pyonex needles with a length of 1.5 mm will be used. Acupressure is performed with GoTravel Acustrap bands.

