### Data collection and management

#### Plans for assessment and collection of outcomes {18a}

Baseline data (gender, age, risk factors for PONV, etc.) is recorded during the preoperative visit. Additional information is recorded during the anaesthetic procedure including the administered medication. Outcomes and medication are assessed during the stay in the postanaesthesia care unit and on the first postoperative day in the ward by the anaesthesia staff of the participating clinics. These include the following tools.

The Postoperative Nausea and Vomiting Intensity Scale (PIS) provides a clinical evaluation of nausea, retching, and vomiting and allows for differentiation between transient and mild nausea symptoms and clinically relevant PONV (see Additional file 2) [24]. The nursing staff fills in the PIS in the PACU and patients themselves complete the PIS on the first postoperative day.

PPP33 is a questionnaire measuring the perioperative quality of life (see Additional file 3). It contains 33 questions. Answers to individual questions are valued from 1 to 4. An overall score—containing eight sub-scales representing eight different dimensions (information, fear, autonomy, pain, physical complaints, rest, communication, accommodation) of the perioperative quality of life—can be calculated. Higher scores indicate a higher quality of life [26, 27].

PON-F is used for the assessment of side effects of antiemetic drug combinations (see Additional file 4). PON-F consists of 38 items representing symptom descriptions organised by body regions. The symptoms and the physical constraints caused by these symptoms can be rated as ‘severe’, ‘moderate’, ‘mild’, and ‘not present’. Additionally, the patient must decide whether the symptom is related to anaesthesia. The objective is to ascertain the antiemetic-related side effects with a focus on their incidence and the simultaneous administration of various antiemetics.

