### Methods for additional analyses (e.g. subgroup analyses) {20b}

Logistic regression will be performed for subgroup analysis concerning group assignment, preoperative risk of PONV and administered antiemetic medication and their effects on PONV.

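### A secondary endpoint attributes side effects causally to antiemetic combinations that the trial does not randomise; it should be worded and analysed as a non-randomised association

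*Protocol article*

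**What the plan says.** Secondary endpoints, third item: "The incidence and severity of adverse reactions caused by the different combinations of antiemetic drugs". The instrument is PON-F.

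Intervention, on the randomisation envelope: "This envelope includes information whether the patient is allocated to the control or the intervention group". Nothing else is randomised.

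Pharmacological antiemetic prophylaxis, on the self-commitment signed before allocation is revealed: "This allows the determination of pharmacological interventions against PONV independent of the result of the randomisation procedure".

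Antiemetic medication, on how the drugs are chosen: the anaesthesiologist is free "to combine drugs of different pharmacologic classes (e.g. due to high individual risk of the patient for PONV". The same section also permits giving no antiemetic at all, and names a low risk as its example. The Abstract and Objectives {7} add that prophylaxis follows local SOPs.

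Plans for assessment and collection of outcomes {18a}, on attribution in PON-F: "Additionally, the patient must decide whether the symptom is related to anaesthesia". The same section gives the aim in more descriptive terms: antiemetic-related side effects, with the focus on how often they occur and on co-administration of several drugs.

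Methods for additional analyses {20b}: the logistic regression concerns group assignment, "preoperative risk of PONV and administered antiemetic medication and their effects on PONV".

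**The concern.** The endpoint asks what drug combinations cause, and the design randomises something else. Because the antiemetic plan is fixed independently of allocation, the P6-versus-control contrast carries no information about one combination against another. That comparison is observational.

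Two features make it vulnerable. Patients at higher PONV risk are the protocol's own example of who gets combined drugs, and patients at lower risk of who may get none. SOPs also differ by hospital, so combination and centre may go together. If risk or centre is also related to the symptoms on PON-F, the combinations will differ in symptom rates even when the drugs do nothing. The attribution item does not repair this: relatedness to anaesthesia does not separate an antiemetic from an opioid or an anaesthetic agent.

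At stake is a drug-safety statement from a trial planned for 3500 patients, which readers could take to have the authority of the randomisation.

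**Working it through.** **The plan's own figure.** The article gives no rate, effect size or power for this endpoint, so there is nothing to reproduce. The check is a comparison of passages, followed by an illustration on assumed inputs.

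**Step 1: is the exposure randomised?** No. Intervention allocates P6 or control, and Pharmacological antiemetic prophylaxis sets the drugs beforehand. Balancing allocation within centres protects the P6 contrast only.

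**Step 2: does exposure depend on patient characteristics?** The text expects it to. Antiemetic medication links combining to high risk and withholding to low risk, as examples. Sample size {14} bases its 25% PONV rate on routine prophylaxis being given at least to patients at increased risk.

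**Step 3: do PON-F symptoms depend on those characteristics?** The documents do not say. This link is an assumption, so a range is shown.

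**Step 4: size if they do.** Total 3500 (2 × 1750, Sample size {14}). Assumed: two equal risk strata and no drug effect. Let s_L and s_H be the symptom rates at low and high risk, and u_L and u_H the share receiving a combination.

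- Rate with a combination: p_c = (u_L·s_L + u_H·s_H) / (u_L + u_H)
- Rate without: p_n = [(1 − u_L)·s_L + (1 − u_H)·s_H] / (2 − u_L − u_H)
- Group sizes: n_c = 3500·(u_L + u_H)/2 and n_n = 3500 − n_c
- z = (p_c − p_n) / √[p_c(1 − p_c)/n_c + p_n(1 − p_n)/n_n]
- Chance of a significant result at two-sided 5%: 1 − Φ(1.96 − z) + Φ(−1.96 − z)

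Worked case: s_L = 0.10, s_H = 0.20, u_L = 0.2, u_H = 0.8. Then p_c = (0.02 + 0.16)/1.0 = 0.18, p_n = (0.08 + 0.04)/1.0 = 0.12, and the risk ratio is 0.18/0.12 = 1.50.

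| s_L, s_H | u_L, u_H | p_c vs p_n | Crude risk ratio | Chance of p < 0.05 |
|---|---|---|---|---|
| 10%, 15% | 50%, 50% | 12.5% vs 12.5% | 1.00 | 5% |
| 10%, 15% | 30%, 60% | 13.3% vs 11.8% | 1.13 | 27% |
| 10%, 20% | 20%, 80% | 18.0% vs 12.0% | 1.50 | 99.9% |
| 10%, 30% | 10%, 90% | 28.0% vs 12.0% | 2.33 | about 100% |

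A different assumed set falls inside this range. Take 3000 patients, half at high risk, combinations in 60% of high-risk and 20% of low-risk patients, and symptoms in 40% and 25%. Then p_c = (0.6 × 0.40 + 0.2 × 0.25)/0.8 = 0.3625 and p_n = (0.4 × 0.40 + 0.8 × 0.25)/1.2 = 0.300. The risk ratio is 1.21, the odds ratio (0.3625/0.6375)/(0.300/0.700) = 1.33, and the chance of significance with 1200 vs 1800 patients about 95%.

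**Step 5: what adjustment does.** In every row the ratio within each stratum is 1.00 by construction (for example 10% vs 10% at low risk). Stratifying on a fully recorded risk measure therefore removes the false difference. With partly recorded risk some of it remains.

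**The case against.** The strongest reply is that this is a matter of wording. Section {18a} describes the aim as the incidence of side effects and co-administration, and the Abstract speaks of detecting them. Both can be met by tabulating symptoms by combination received. No section commits to a crude test between combinations. That stands, and it rules out a reading that might tempt: that the design cannot address the objective at all. It can describe incidence and severity by combination; it cannot attribute differences to the drugs through randomisation.

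Other inferences a reader might draw also lack support:

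- **Rescue drugs create reverse causation.** Nothing says that rescue antiemetics will be pooled with prophylaxis to define a combination; Data management {19} lists them separately. The endpoint does not limit combinations to prophylaxis, so this is worth fixing, but it is not a stated error.
- **Patients cannot attribute symptoms because they do not know their antiemetics.** The article conceals P6 allocation from patients, and says only that the ward visitor is without knowledge of the medication.
- **PON-F has no baseline and no other attribution item.** The form and the timeline table are not shown in full.
- **No adjusted PON-F model is planned.** The regression in {20b} targets PONV, but a model for side effects could properly stand in an analysis plan that is not shown.
- **Drugs are chosen by PONV risk.** Risk is given as an example, and SOPs also matter. This widens the problem to centre.

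None of this removes the causal wording. An analysis plan could supply adjustment, but an adjusted observational comparison is still an association unless unmeasured confounding is assumed away.

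**Conclusion.** The point holds as one of wording and interpretation in a secondary endpoint. The protocol fixes a causal quantity that its randomisation does not identify, and the attribution item described for PON-F does not supply the missing link to antiemetics.

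The size is unknown. The crude risk ratio with no drug effect is 1.00 if combination use is unrelated to risk and reaches about 2.3 in the most extreme case examined. A reader might infer from the planned sample that a false signal is certain to be significant. The documents do not support that: symptom rates and prescribing patterns by risk are not given, the chance ranges from 5% to about 100% over the assumed inputs, and several distinct combinations would mean smaller groups than the two-way split used here. Smaller groups would make the tests less sensitive but would not reduce the bias.

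The comparison of P6 with control, and with it the primary analysis, is not affected.

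**What to change.** 1. Reword the endpoint to *symptoms associated with antiemetic combinations (non-randomised, exploratory)*, and report it in those terms.
2. Define combinations by the prophylaxis in the signed self-commitment made before allocation. Keep rescue antiemetics out of the exposure definition, because the primary endpoint counts need for an antiemetic as PONV.
3. Adjust any comparison between combinations for the recorded PONV risk factors, anaesthetic technique and centre. Total intravenous anaesthesia stands in the same list as the drugs, so state that it is a covariate and not part of a combination.
4. Optionally, report PON-F by randomised arm. That contrast is protected by randomisation, but it concerns P6, not the drugs.

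Cost: a wording change and one extra regression on data already collected. The claim weakens to an association and still rests on there being no important unmeasured confounding. Some patients will be classed under a plan that was not followed in full; the article says deviations are documented, so their number can be reported.

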### Participant timeline {13}

The participant timeline is presented in the following table.

### Sample size {14}

Sample size calculation assumes a baseline incidence of PONV of 25%. This number is lower than reported in surveys on PONV with 29% [25] but considers routine pharmacological prophylaxis, at least in patients with increased risk for PONV.

A Cochrane review by Anna Lee [17] suggests that P6 stimulation can reduce PONV by approximately 30% (relative risk reduction), leading to a PONV-incidence in the treatment group of 17.5%. The trial is powered to detect an absolute reduction of 5% points (from 25 to 20%). This conservative estimation of P6 treatment considers that efficacy will not be as perfect as in efficacy trials, e.g. due to inconsequent or erroneous administration of the P6 stimulation. Power analysis was performed with PASS 2002 (Number cruncher software) and revealed that 1503 patients provide a power of 80% to detect an absolute 5% point difference with a type I error of 5% using the two-sided Fisher’s exact test. With an added safety margin of about 15% compensating for dropouts, etc. 2 × 1750 patients must be included.

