### Assignment of interventions: allocation

#### Sequence generation {16a}

Randomisation is performed as block randomisation with permuted blocks of variable length by staff members of the coordinating study centre. Random numbers are obtained from www.random.org. Each individual set of randomisation envelopes contains 50% of each group for equal distribution of the groups per centre. An Excel® Spreadsheet was created with 45 sets of 100 randomisations each. For each set, a random number of blocks with a random and even-numbered length were created.

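### 1503 patients per group give about 90% fixed-design power, not the stated 80%, and the sentence omits that 1503 is per group

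*Protocol article*

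**What the plan says.** All the inputs stand in the protocol article, mostly under Sample size {14}.

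- Control incidence: "Sample size calculation assumes a baseline incidence of PONV of 25"%, and the target is an absolute reduction of 5 points, to 20%.
- Claim: the analysis "revealed that 1503 patients provide a power of 80% to detect an absolute 5% point difference with a type I error of 5"%.
- Test: "with a type I error of 5% using the two-sided Fisher’s exact test".
- Final size: "With an added safety margin of about 15% compensating for dropouts, etc. 2 × 1750 patients must be included".
- Allocation, from Sequence generation {16a}: "Each individual set of randomisation envelopes contains 50% of each group for equal distribution of the groups per centre", so 1:1.

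The section does not say whether 1503 is per group or in total, and it does not mention an interim analysis. Interim analyses {21b} separately plans one look after 1750 patients. It uses severity of PONV and ends the study for futility if p ≥ 0.1.

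**The concern.** Effect, alpha, sidedness, test, sample size and power are all printed, so the claim can be checked without any outside source. It does not reproduce. For 25% versus 20%, 80% power needs clearly fewer than 1503 per group, and 1503 is almost exactly the familiar 90% answer.

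What is at stake is the type II error that the trial declares. The article implies 20%, while its own inputs give 10% for a fixed design. A reader of a null result would misjudge how strongly it counts against a 5-point benefit. The futility rule also has to be judged against a known starting power, and the article gives the wrong one. Finally, the text leaves open whether the target was 80% or 90%; only the sponsor can settle that.

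**Working it through.** **Inputs.** p₁ = 0.25, p₂ = 0.20, difference 0.05, two-sided alpha 0.05, Fisher's exact test, 1:1 allocation, stated n = 1503, stated power 80%.

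**Step 1: is 1503 per group?** 1750/1503 = 1.164, and 1 − 1503/1750 = 14.1%. Both fit a margin of about 15%. Adding 15% gives 1503 × 1.15 ≈ 1729, and allowing for 15% loss gives 1503/0.85 ≈ 1769; 1750 lies between them. A total of 1503 cannot lead to 2 × 1750. So 1503 is per group, or 3006 in all.

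**Step 2: try to reproduce 80% by formula.** Let p̄ = 0.225.

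n = [z₀.₉₇₅ √(2p̄(1−p̄)) + z_power √(p₁(1−p₁) + p₂(1−p₂))]² / (p₁−p₂)²

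Here √(2 × 0.225 × 0.775) = 0.5906 and √(0.1875 + 0.16) = 0.5895.

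- 80%: (1.960 × 0.5906 + 0.8416 × 0.5895)² / 0.0025 = 1093.7
- 90%: (1.960 × 0.5906 + 1.2816 × 0.5895)² / 0.0025 = 1463.7

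The continuity correction, which approximates Fisher's test, is n′ = (n/4)[1 + √(1 + 4/(n × 0.05))]².

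- 80%: n′ = 1133.4, so 1134 per group
- 90%: n′ = 1503.4

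The printed 1503 therefore matches the 90% result, not the 80% result. One-sided versions do not rescue the claim: 80% power would then need 862 per group uncorrected or 901 corrected.

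**Step 3: exact power.** Power of the two-sided Fisher test was computed by summing, over all pairs of binomial outcomes, the probability of those with p ≤ 0.05.

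| Per group | Exact power, fixed design |
|---|---|
| 1134 | 80.1% |
| 1487 (1750 less 15%) | 89.7% |
| 1503 | 90.0% |
| 1750 | 93.9% |

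The pooled normal approximation at 1503 per group gives 90.7%, so the choice of method does not explain the gap. The discrepancy is 90.0 − 80 = 10 points.

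**Step 4: effect of the futility stop (illustration).** The interim uses PONV severity, whose power cannot be computed from the article. Assume instead that the interim test behaves like the incidence test, with one look at half the sample and a stop if p ≥ 0.1. Simulated overall power is the chance of passing the interim and then reaching p < 0.05 at the end:

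| Final per group | Overall power |
|---|---|
| 1134 | about 58% |
| 1503 | about 71% |
| 1750 | about 78% |

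**The case against.** Four things can fairly be said on the other side.

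**The error runs in the safe direction.** Correcting it leaves sample size, endpoint, test and alpha untouched. This stands, and it limits the harm. It does not make the printed figure true.

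**The match at 1503.4 suggests a calculation run at 90% and misreported, not a wrong sample size.** This is the likely explanation, but the article does not show it, so the sponsor has to confirm the target.

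**The 80% might already allow for the interim stop.** The text does not support this. It ties 80% to the Fisher calculation at 1503 and mentions no interim. The illustration gives about 71% at 1503 per group, not 80%.

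**True power is not shown to be 90% either, because the design is not fixed.** This also stands. The 90% must be labelled as fixed-design power, and the overall figure reported separately.

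Three stronger readings are tempting, and the article does not support them.

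- A reader might take 1503 literally as the total, which gives only about 62% to 64%, and conclude that the trial is underpowered. The step to 2 × 1750 excludes that reading.
- A reader might conclude that, if 80% was the target, about 830 fewer patients would be enough. But 1134 per group meets 80% only without the futility rule; under the assumption above it gives about 58%.
- A reader might suppose that later decisions in the trial were built on the 80%. No section says so, and the interim rule does not refer to it.

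**Conclusion.** The stated power is wrong as written. On the article's own inputs, 1503 per group gives 90.0% power, 10 points above the stated 80%, and the stated type II error is twice the fixed-design value. The omission of the per-group qualifier is a second, smaller defect in the same sentence.

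The result rests on the printed incidences of 25% and 20%, a two-sided 5% level, Fisher's exact test, 1:1 allocation and no interim stop. Under those conditions the trial is not underpowered. The interim figures rest on a further assumption, that the severity test behaves like the incidence test, and are indicative only. They show that the effect of the futility rule may be large enough to need reporting; they do not establish the trial's actual overall power.

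**What to change.** 1. Restate the sentence under Sample size {14}: 1503 patients per group (3006 evaluable) provide 90% power in a fixed design to detect 25% versus 20% with a two-sided Fisher's exact test at 5%. The sponsor should confirm that 90% was the target used in the software run.
2. Keep 2 × 1750.
3. Report separately the overall power after the futility rule in Interim analyses {21b}, with the assumed relation between the severity test and the incidence test stated.

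The first change costs one sentence. The third needs a short simulation. Neither adds patients or alters the conduct of the trial.
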